Currently 200 patients are diagnosed each year in the Forth Valley Intermittent Claudication clinic. A sample size calculation carried out using GPower3 [17], indicates that to carry out a (2) group by (2) time mixed ANOVA to detect a small effect size (0.2) with an alpha of 0.05, and a power of 80%, the trial would require 26 participants in each condition. A small effect size of 0.2 was selected in the sample size calculation based on a previous study of an exercise program for physical activity in patients with IC which measured walking outcomes using pedometers [18]. The sample size calculation was based on the conservative initial (2) time point (baseline to 4 month) mixed ANOVA to increase the likelihood that the study was adequately powered to identify an initiation of walking behaviour change. A (4) time point mixed ANOVA sample size calculation required fewer participants in the study, and therefore the larger, initial (2) time point, more conservative sample size calculation was used. The sample size calculation was based on changes in the primary outcome measure. As this is a pilot study, a further aim is to determine the effect sizes achieved in the secondary outcome measures, to help inform the sample size calculation for a larger, more definitive study. Based on a previous study with patients from this population recruited at outpatient clinic, we estimate that 25% of people may decline to participate in the study. Likely attrition rate from the study for this population is unknown, therefore we have estimated a 10% attrition rate during the trial. We therefore aim to invite 80 patients to participate in the trial, of whom we expect 60 to agree to participate, and a further 6 to drop-out during the course of the trial. Based on typical numbers presenting at the clinic who are diagnosed with claudication, recruitment is estimated to take place at the rate of 2 participants/week.

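### The figure of 26 per arm reproduces, but it buys 80% power for a difference in change of about 0.8 SD, not for a small effect

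*Protocol article*

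**What the plan says.** The protocol article (Methods/Design, Recruitment) sizes the trial on the primary outcome, mean daily steps, using GPower3. The calculation is "to carry out a (2) group by (2) time mixed ANOVA" from baseline to 4 months. With a two-sided-equivalent F test, the requirement reads as follows: "detect a small effect size (0.2) with an alpha of 0.05, and a power of 80%, the trial would require 26 participants", counted per arm. The effect is described twice as small: once in the calculation itself, and again where its source is given, "A small effect size of 0.2 was selected in the sample size calculation based on a previous study of an exercise program" that measured walking by pedometer. The section adds that a four-time-point version needed fewer participants. The two-time-point version was kept "to increase the likelihood that the study was adequately powered to identify an initiation of walking behaviour change".

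The article does not say on which scale 0.2 is measured. It gives no correlation between the repeated measures, no SD of daily steps and no target difference in steps. It plans to recruit 60 and expects to lose 6.

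**The concern.** The value 0.2 is conventionally small when it is a standardised mean difference (Cohen's d). GPower's ANOVA routines take Cohen's f, for which the conventional small value is 0.10. Two arms of 26 are also far fewer than one expects for any small between-group difference. So either the number of participants or the description of the effect has to be wrong.

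What is at stake is how the 4-month result will be read. The Evaluation section says analysis of the primary outcome will show whether the intervention increased walking. A reader who takes the power statement at face value could treat a null result as evidence against a small benefit. The article also says, in Framework and in Analysis, that this pilot will supply the effect size for a larger multi-centre trial. An effect size whose scale is unclear is an unsafe input to that calculation.

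**Working it through.** **Inputs.** From Recruitment: 2 groups, 2 time points, effect size 0.2, alpha 0.05, power 80%, 26 per arm (N = 52). Assumed, because the article does not state them: the effect tested is the group-by-time interaction, and the correlation ρ between baseline and 4 months is 0.5, with 0 to 0.8 as the range.

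**Step 1: reproduce the plan's figure.** For the interaction with m time points and k groups, the noncentrality is λ = N·m·f²/(1 − ρ), with (k − 1)(m − 1) and (N − k)(m − 1) degrees of freedom. With f = 0.2, N = 52, m = 2 and ρ = 0.5:

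λ = 52 × 2 × 0.04 / 0.5 = 8.32, on 1 and 50 df, so power = 80.7%.

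N = 50 gives 79.1%, so 52 is the smallest even total that reaches 80%. With four time points and the same f and ρ, N = 36, which agrees with the remark that fewer would be needed. Dropout is covered: 52/0.9 = 57.8, rounded up to 58, against a target of 60. If 0.2 is instead a d on the change score, 394 per arm are needed, so 26 does not reproduce. The calculation that was run is therefore very probably f = 0.2 with ρ = 0.5.

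**Step 2: translate f into a difference in change.** Let δ be the between-group difference in mean change and σ the SD of daily steps. In a two-by-two design each of the four cells carries an interaction effect of ±δ/4, so f = δ/(4σ) and δ = 4 × 0.2 × σ = 0.8σ. The SD of the change score is σ√(2(1 − ρ)), which equals σ when ρ = 0.5. At that correlation, f = 0.2 is thus 0.8 SD in either unit. As a cross-check, a two-sample t test on change scores with 26 per arm and a 0.8 SD difference also gives 80.7%. The difference detectable with exactly 80% power is 0.79 SD of the change score.

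**Step 3: power for smaller effects (N = 52, ρ = 0.5, so λ = 208·f²).**

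| Difference in change | f | λ | Power | Total N for 80% |
|---|---|---|---|---|
| 0.8 SD | 0.20 | 8.32 | 81% | 52 |
| 0.5 SD | 0.125 | 3.25 | 42% | 128 |
| 0.4 SD (conventional small f) | 0.10 | 2.08 | 29% | 200 |
| 0.2 SD (conventional small d) | 0.05 | 0.52 | 11% | 788 |

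With the 54 expected to remain (60 − 6), the four powers are 82%, 44%, 30% and 11%.

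**Step 4: does another correlation rescue the word small?** In SDs of the change score, 26 per arm detects 0.79 whatever the correlation. In SDs of daily steps the figure depends on ρ:

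| ρ | 0 | 0.3 | 0.5 | 0.7 | 0.8 |
|---|---|---|---|---|---|
| Detectable difference, SDs of daily steps | 1.12 | 0.94 | 0.79 | 0.61 | 0.50 |
| Total N for 80% power at f = 0.10 | 396 | 278 | 200 | 120 | 82 |

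Even at ρ = 0.8 the detectable f is 0.50/4 = 0.125, above 0.10, and a small f would need 82 in total rather than 52.

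**The case against.** The strongest reply is that the calculation is correct. The software and the design are named, and 26 per arm comes out exactly. That stands: a reader might infer that the sample size was miscalculated, and it was not.

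A reader might also infer that the trial has only 11% power for its own target. That would require 0.2 to be a d. The article never says so, and 26 does not reproduce on that scale. The 11% describes sensitivity to one conventionally small effect; it is not the power of the planned calculation.

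Nor can it be said that the authors took the label from one scale and the number from another. That is a plausible explanation, but the 0.2 is attributed to a pedometer study that is not available here, and its metric is unknown.

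The missing correlation is not a fault in itself, since a journal article commonly leaves such inputs to the full protocol. It matters here only because the size of the detectable effect in daily steps depends on it.

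Finally, this is a pilot whose stated aims include recruitment, retention, acceptability and preliminary efficacy, and the remark about adequate power explains the choice of two time points over four without mentioning a small effect. The article nowhere says that a null result will rule one out. This lowers the weight of the point. It does not remove it, because the article still claims 80% power for a small effect on its primary outcome.

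**Conclusion.** The sample size stands; its description does not. No reading makes small, 0.2, 80% and 26 true together. If 0.2 is f, the 26 is right and the effect is a large one, about 0.8 SD of the change score. For a small effect, power is about 29% (f = 0.10) or 11% (0.2 SD of change).

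The 0.8 SD of the change score does not depend on the correlation as a statement of what 26 per arm can detect. It equals 0.8 SD of daily steps only at correlation 0.5. The percentages for smaller effects assume correlation 0.5 and a test of the group-by-time interaction. The difference in steps cannot be given here, because the article reports no SD.

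This is a misdescribed effect size and power claim, of moderate severity given the pilot purpose.

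**What to change.** Keep the target of 60 and change the Recruitment text:

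- Delete the word small in both places where it qualifies 0.2.
- State the metric, the correlation and what they mean. If the sponsor confirms that f and 0.5 were used, wording such as this would do: *Twenty-six participants per arm give 80% power for Cohen's f = 0.2 for the group-by-time interaction, assuming a correlation of 0.5 between baseline and 4 months. This is a between-group difference in change of about 0.8 SD. Power is about 42% for a difference of 0.5 SD and 11% for 0.2 SD.*
- Add the equivalent difference in daily steps, with the SD used and its source.
- Say that a non-significant 4-month result would not exclude small or moderate effects.
- Confirm that the 0.2 taken from the cited pedometer study is on the same f scale. If it is not, report the power of 26 per arm for that study's effect on the scale actually used.

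The cost is rewording only, with no extra participants and no change to design or analysis. The downside is that the trial's stated sensitivity becomes less favourable.

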### Inclusion Criteria

Patients presenting to the Forth Valley Vascular Outpatient Clinic, newly diagnosed with IC in one or both legs will be recruited into the study. A diagnosis of lower limb arterial disease causing intermittent claudication will be established by a vascular assessment nurse or consultant surgeon. This will be based on a combination of investigations including post-exercise ABPI of below 0.9 [6], and duplex ultrasound, magnetic resonance angiography (MRA) or computerised tomography angiography to provide an anatomic view of the arteries.

### Exclusion Criteria

We will only exclude people who are unable to give informed consent (e.g. due to dementia) or for whom it may be medically unadvisable to increase their daily walking, including patients with heart failure, cancer, patients who cannot walk unaided or patients with a history of orthopaedic surgery which affects walking. Patients with an ABPI of less than 0.35 will also be excluded as they are likely to be offered emergency surgery.

### Design

This is a pilot randomised controlled trial with patients newly diagnosed with IC randomly allocated to one of two groups. Allocation to group will be carried out by the researcher, who will use a computer generated random number table for allocation (http://www.randomizer.org/). The computer generated random number table was created at the start of the study by a research colleague, who is not involved in participant recruitment or allocation. The researcher will assign consecutive participant numbers to patients as their names are sent to her by the Vascular Assessment Nurse, each participant number will then correspond to a treatment group as established in the computer generated random number table. The researcher will therefore assign participants to groups before she has made any contact, and before she has received any information about them other than their name and phone number. Participants allocated to the control condition will receive usual care. Participants allocated to the intervention group will receive usual care and a brief, 2-session psychological intervention. The Vascular Assessment Nurse who provides usual care at diagnosis, and who recruits participants, will be blind to participant allocation to groups. Other clinical staff in contact with participants during their care, e.g. Vascular Technologists and Vascular Surgeons will be blind to participant allocation to groups. A CONSORT flowchart of the trial design is shown in Figure 1.

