### Intervention

Participants in the intervention group will receive 9 visits from the researcher in their own home, including 4 visits to complete questionnaires, 2 one hour intervention sessions, and 3 other visits to drop off or pick up pedometers.

#### Session 1

The researcher will elicit any maladaptive beliefs the participant has about their illness, or about walking. Information will be provided about the consequences of the illness, and about the behaviour-health link in order to modify illness and walking beliefs. Motivational interviewing techniques will be used to deliver the intervention, asking open questions, prompting the participant to make self-motivating statements and evaluations of their own walking behaviour and aiming to move participants to a point where they have expressed motivation or intention to change their walking behaviour. A copy of the schedule used to guide the discussion in Session1 is provided in Additional File 1.

#### Session 2

The researcher will work with the participant to draw up an individualised walking action plan, based on the recommendation of walking to near maximal pain three times a week [8]. Participants will be encouraged to think about how they can adapt their daily routines to incorporate a half hour of continuous walking, and will also be encouraged to think of possible barriers which may prevent them from following their action plan, and strategies to cope with these barriers. Sniehotta et al [19] found that a combination of action planning and coping planning led to much greater improvement in physical exercise than action planning alone. Action plans will then be typed up and laminated, and posted out to participants. A copy of the template for an action plan is provided in Additional File 2.

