### Outcome Measures

Measures will be taken for participants in both arms of the study, at baseline, 4 months, 1 and 2 year follow-ups. All questionnaires will be administered by the researcher.

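### Allocation comes before baseline, so baseline and all later questionnaires are taken by a researcher who knows the arm and delivers the intervention

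*Protocol article*

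**What the plan says.** All references are to the protocol article.

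- **Who allocates (Design).** "Allocation to group will be carried out by the researcher, who will use a computer generated random number table for allocation". The table itself was "created at the start of the study by a research colleague, who is not involved in participant recruitment or allocation".
- **How and when (Design).** "The researcher will assign consecutive participant numbers to patients as their names are sent to her by the Vascular Assessment Nurse". The section concludes that "The researcher will therefore assign participants to groups before she has made any contact". It adds that at this stage all she holds on each patient is a name and a telephone number.
- **Who recruits (Design, Recruitment).** The Vascular Assessment Nurse invites consecutive patients at diagnosis. She is described as the person "who recruits participants, will be blind to participant allocation to groups". Other clinical staff are also blind. No blinding statement covers the person who collects the measures.
- **Who treats (Intervention).** "Participants in the intervention group will receive 9 visits from the researcher in their own home". These include both intervention sessions and the four questionnaire visits. Under Control, the same researcher makes eight visits to each control participant.
- **Who measures (Outcome Measures, Telephone Calls).** Measures are taken at baseline, 4 months, 1 year and 2 years. "All questionnaires will be administered by the researcher". At 6 and 12 weeks the researcher phones both groups for five ratings of health, quality of life, pain and walking distance. In the intervention group the same call reviews the action plan.
- **What is analysed (Analysis).** Two groups by two time points for the short term and two groups by four for the long term, with baseline as one of the time points.

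**The concern.** Allocating before contact stops the researcher from steering patients between arms according to what she learns about them. It also means that she knows the arm before she asks the first belief or quality-of-life question and before the participant is introduced to the pedometer.

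Three things are at stake:

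1. The planned effect is a difference in change from baseline. If baseline is recorded differently in the two arms, the estimate moves.
2. A patient who withdraws between allocation and baseline already belongs to an arm but has no baseline data. Such losses may differ by arm, and retention is itself something the pilot is meant to estimate (Framework).
3. Belief and quality-of-life answers are given face to face to the person who has tried to change those beliefs. Answers shaped by that relationship could look like mediation.

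The pilot's effect size is intended to inform the sample size of a larger trial, so any bias would carry forward.

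**Working it through.** **Order of events.** This follows from the text without calculation.

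1. The nurse recruits and sends a name (Design).
2. The researcher gives the next number, which fixes the arm, before any contact (Design).
3. The first researcher contact, the baseline questionnaires and the baseline pedometer week follow, because the researcher administers the questionnaires at home visits (Outcome Measures, Intervention, Control).
4. The same person delivers the sessions, makes the calls and administers the follow-up questionnaires.

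Step 2 precedes step 3, so baseline is taken after allocation by someone who knows the arm.

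**The plan's own sample size.** Inputs from Recruitment: effect size f = 0.2, alpha 0.05, power 80%, 2 groups, 2 time points, 26 per group. The correlation rho between time points is not given; 0.5 is assumed here.

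- Noncentrality for the group-by-time interaction: lambda = f² × N × m / (1 − rho) = 0.04 × 52 × 2 / 0.5 = 8.32, with 1 and 50 degrees of freedom.
- Power is 0.807, and N = 52 is the smallest even total that reaches 80%. This reproduces the stated 26 per group.
- With two time points this is a two-sample comparison of change scores, for which lambda = (n/2) × delta². So delta = √(8.32 / 13) = 0.8 SD of the change score.

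**Effect of a baseline shift.** Suppose recorded baseline in the intervention arm is displaced by b relative to control, with no such displacement at follow-up. The estimated difference in change is then displaced by b in the opposite direction. A displacement that was equal at every time point would cancel, so b is the net amount. The documents give neither a size nor a direction, so the values below are assumptions, in SDs of the change score.

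| Assumed net shift b | Bias in effect | Share of 0.8 SD | Two-sided 5% error rate becomes |
|---|---|---|---|
| 0.1 | 0.1 SD | 0.1/0.8 = 12.5% | about 0.07 |
| 0.2 | 0.2 SD | 0.2/0.8 = 25% | about 0.11 |

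The error rates use a normal approximation with 27 per arm (60 recruited less 6 lost, divided by 2) and a displacement of the test statistic of b × √(27/2) = 3.67b. The 0.8 SD depends on rho = 0.5; at other correlations, 26 per group is not the number that f = 0.2 requires (total N would be 72 at rho = 0.3 and 32 at rho = 0.7).

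**Which measures are exposed.** Quality of life, beliefs, self-reported walking and the telephone ratings are asked by the researcher, so her knowledge of the arm acts directly. Steps come from a device the participant wears for a week (Primary Outcome). Influence there runs only through instruction, encouragement and handling of the pedometer.

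**Does a later allocation fit the visits?** Controls have 4 questionnaire visits + 4 pedometer visits = 8. The intervention arm has 4 questionnaire visits + 2 sessions + 3 pedometer visits = 9. The intervention arm has one pedometer-only visit fewer, which is consistent with session 1 taking place at the baseline pedometer pick-up. The article does not say so explicitly.

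**The case against.** The strongest reply is that the procedure is a genuine safeguard. Concealment protects the decision to enrol, and that decision belongs to a blind nurse who invites consecutive patients. The list came from an independent colleague, and the researcher has only a name and phone number when she assigns the next number. This stands. A reader might infer from the researcher's use of the table that concealment is lost; the documents do not support that. What remains is narrow: no sealed or third-party release is described, and nothing described prevents reordering when several names arrive together.

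Three further points also stand:

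- A reader might infer that the researcher's knowledge directly contaminates the primary outcome. Steps are counted by a worn device, and the article gives no specific reason to expect a shift in steps that differs by arm.
- A reader might infer that losses before baseline break intention to treat. They are a missing-data problem that may differ by arm. The plan commits to intention to treat and allows for 10% attrition. Nor can allocation before consent be asserted: the text does not say when written consent is taken, and the flowchart is not available here.
- The bias sizes are assumed, and in a small single-centre pilot with one researcher described some unblinded contact is hard to avoid.

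These points limit the concern without answering it. The safeguard covers the assignment step. It does not cover what is measured, or who is lost, afterwards.

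**Conclusion.** The concern holds in this form: baseline questionnaires and the introduction of the baseline pedometer week come after allocation and involve the unblinded researcher who also delivers the intervention, and she administers all later questionnaires and telephone ratings. This is a stated procedure, not a detail left to a fuller document.

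The risk is most direct for quality of life and the belief measures used as mediators, and indirect for steps. Its size and direction are unknown. For illustration, a net shift of 0.1 to 0.2 SD of the change score would bias the change-score effect by 0.1 to 0.2 SD, or 12.5% to 25% of a 0.8 SD detectable difference. That share rests on the assumed shift and on rho = 0.5. Selection at recruitment is largely protected.

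The plan should be changed, since the correction is simple and a distorted baseline cannot be reliably repaired in the analysis. The point does not invalidate the pilot.

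**What to change.** 1. **Hold the table elsewhere and release it later.** The research colleague who created the table keeps it. Each arm is released, by sequentially numbered sealed opaque envelope or by email on request, only after the baseline questionnaires and the baseline pedometer count are complete. The natural moment is the baseline pedometer pick-up, where session 1 can start for those allocated to the intervention. This also removes losses between allocation and baseline, and closes the small opening for reordering names.
2. **Reduce the researcher's part at follow-up.** Have questionnaires completed by the participant and sealed, with help given only on request and logged.
3. **State what remains.** The researcher stays unblinded for follow-up pedometer visits and telephone ratings, and participants know what they have received. The second step is therefore only a partial safeguard, and the protocol should name this as a limitation.

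**Cost.** One envelope or email per participant from a colleague already involved, minor changes of wording, and possibly a few more missing questionnaire items. No extra staff are needed, and the stated visit counts suggest no extra visits. The sample size is unaffected.
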